6.2.3 Progression of Symptoms

Participants who experience a recurrence or significant worsening of CNS signs or symptoms (see section 6.3.9) should be evaluated according to sections 6.1.2 and 6.1.3 of the SoE of this protocol and managed according to section 10 of the A5225/HiFLAC MOPS. The evaluations listed in the sections noted above should be conducted if the recurring or progressing symptoms are severe and persistent enough to be outside the variations in clinical response to successful CM therapy.

6.2.4 Premature Treatment or Study Discontinuation

Confirmatory HIV Test/Qualifying CSF culture

If **any of the following is true in the given time frame, then** the participant will be discontinued from study treatment, followed for up to 2 weeks, and then discontinued from the study**:**

- the confirmatory HIV test is negative
- the qualifying CSF culture is negative after 2 weeks of incubation
- **a confirmatory CSF antigen titer is negative by Day 5 AND no positive result from the qualifying CSF culture is obtained through Day 4**
- a study entry quantitative culture was required but not performed

In such cases, the participant will be treated as deemed appropriate by his/her primary physician. These participants should complete the evaluations in the Premature Treatment or Study Discontinuation column in the SoE at the time of treatment discontinuation and again approximately 2 weeks later, for study discontinuation; no fluconazole trough PK sample should be collected at these participants’ study discontinuation visit.

Premature Treatment Discontinuation

All participants who prematurely discontinue study treatment (see section 8.1) at any time during the study should complete the Premature Treatment or Study Discontinuation evaluations (per the SoE) within one week after treatment discontinuation. With the exception of participants randomized to ampho B who prematurely discontinue ampho B in Step 1 and who are eligible to register to Step 2, participants who prematurely discontinue study treatment will remain on the step they are on at the time of treatment discontinuation (without registering to subsequent steps) and will continue to be followed on study, off treatment per the SoE, except as noted in sections 6.3.22 and 6.3.24.

Premature Study Discontinuation

Participants who discontinue the study prematurely (see section 8.2) should complete the Premature Treatment or Study Discontinuation evaluations (per the SOE) at the time of study discontinuation.

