6.2.2 On-Study Evaluations

Entry

On-study evaluations are performed only after a participant is enrolled into the study. However, the following evaluations do not need to be repeated at entry if performed within 72 hours prior to entry: CD4 cell count, plasma HIV-1 RNA, LP with opening pressure recorded, CSF cryptococcal antigen test, CSF cultures initiated (quantitative and qualitative), CSF analyses, and stored CSF sample. Storage of a cryptococcal isolate from CSF collected at screening or entry is sufficient.

Participants must begin study-assigned treatment within 72 hours after entry, however, initiation of study-assigned treatment within 24 hours after entry is strongly encouraged.

Post- Entry

The visit schedule through day 7 should be based on the first day of treatment (day 1 = first day after first dose of fluconazole or ampho B-based regimen), not solely on the date of enrollment. The visits listed for Days 4 through 7 should be completed ± 1 day of those time points as indicated in the SoE, section 6.1.2 and 6.1.3.

The week 2 visit should occur on day 14, but may be completed 12-17 days after initiation of study treatment.

The weeks 4-10 visits should occur on the week noted in the SoE, but may be completed ± 3 days as indicated in the SoE, sections 6.1.2 and 6.1.3. The week 24 visit may be completed ±7 days of that week, as indicated in sections 6.1.2 and 6.1.3. Note that for participants whose previous CSF culture was positive, at least 14 days must elapse between visits.

Step 1 (Induction)

Participants are expected to remain on Step 1 from 2 to 10 weeks depending on the treatment to which they are randomized and their response to that treatment. Participants randomized to ampho B will register to Step 3 after approximately 2 weeks of ampho B treatment. Some participants taking ampho B may register to Step 2 (see below) before entering Step 3.

Participants randomized to fluconazole will remain in Step 1 until week 10 or until a CSF culture is negative, whichever is earlier.

Step 2 (Induction Following Amphotericin B Deoxycholate Intolerance)

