6.3.1 Documentation of HIV Status

HIV-1 infection will be documented as described in section 4.1.3.

If the confirmatory test of the HIV status reported at screening is negative, the participant must discontinue study treatment and be followed as described in section 6.2.4, above, to monitor any toxicity.

- - 1. Documentation of CM Status

CM must be documented either by a positive CSF cryptococcal culture **or** a **locally licensed** positive CSF India ink preparation, or a positive CSF cryptococcal antigen latex agglutination test within 7 days prior to entry. **A positive CSF India ink or cryptococcal antigen latex agglutination test received from a referring laboratory must be confirmed within 5 days after study entry by CSF antigen testing from an approved laboratory or with a positive entry CSF culture by Day 5.**

**If the confirmatory test of CM is negative, the participant must be discontinued from study treatment immediately, referred immediately to his/her health care provider for appropriate management, and be followed as described in section 6.2.4, above, to monitor for any toxicity.**

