6.3.18 CSF Cryptococcal Antigen

Detection of CSF cryptococcal antigen will be performed at screening or entry using a latex-Cryptococcus antigen detection system **and should be positive within after study entry or the participant is to be discontinued (see section 6.2.4). A negative CSF antigen titer by latex agglutination will not exclude the participant if the entry CSF culture is positive for *C. neoformans*.** A 2-fold titer will be reported.

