6.3.21 Mandatory CSF Cultures

**To remain in the study, participants’ qualifying CSF culture must be positive by Day 4 if a confirmatory CSF cryptococcal antigen titer by latex agglutination is not positive by Day 5.**

During screening or at study entry and again at week 2, a CSF sample for culture must be obtained from all participants. Each time a CSF sample for culture is required, both a qualitative and a quantitative culture must be performed (see instructions in section 2 of the A5225/HiFLAC MOPS).

Additional CSF samples may be required based on participants’ response to study treatment. See section 6.3.22, below.

CSF collection and cultures must be performed at the Progression of Symptoms visit.

Wherever possible, CNS imaging should be performed at the same time that CSF samples are obtained for evaluation of progression of symptoms.

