## 8.0 CRITERIA FOR PREMATURE TREATMENT OR STUDY DISCONTINUATION

### 8.1 Treatment Discontinuation

- **Failure to have CM confirmed by Day 5 by testing performed at a DAIDS-approved laboratory**
- Fluconazole-related dose-limiting or ampho B-related treatment-limiting toxicity (see section 7.0, Clinical Management Issues or section 5.0, A5225/HiFLAC MOPS).
- Pregnancy or breast-feeding (for fluconazole).
- Interruption of oral fluconazole for any reason for more than 3 consecutive days.
- Requirement for prohibited concomitant medications (see current A5225/HiFLAC MOPS).
- Clinical reasons believed life threatening by the physician, even if not addressed in the clinical management section of the protocol.

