### Study Discontinuation

- Negative screening CSF culture and/or confirmatory HIV status screening results

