**A negative screening CSF culture is defined as**

- **a negative culture after 2 weeks of incubation even in the setting where the CSF antigen testing is positive by latex agglutination from a referring laboratory**

**or**

- **a negative culture after 5 days of incubation if there is no yeast found on culture and there is a negative CSF antigen test by the latex agglutination method by Day 5 from an approved laboratory.**.
- Failure to obtain a quantitative CSF culture at screening or entry.
- Failure to initiate study treatment within 72 hours after entry.
- Initiation of NVP prior to fluconazole dose reduction to ≤ 400 mg daily
- Request of the primary care provider if s/he thinks the study is no longer in the best interest of the participant.
- Failure by the participant to attend three consecutive clinic visits.
- Request by the participant to withdraw.
- Participant judged by the investigator to be at significant risk of failing to comply with the provisions of the protocol as to cause harm to self or seriously interfere with the validity of the study results.
- At the discretion of the Office for Human Research Protections (OHRP), Food and Drug Administration (FDA), NIAID, ACTG [including the Study Monitoring Committee (SMC)], local IRB/EC or other regulatory authority, industry supporter, or investigator.

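### With a negative confirmatory antigen, Protocol 6.2.4 and 6.3.21 require a positive culture by Day 4, while 6.3.2 accepts one by Day 5

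*Protocol*

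**What the plan says.** The note to Protocol 4.1.1 allows enrolment on a referring laboratory's result alone, provided CM is confirmed by Day 5 at a laboratory in external quality assessment. Several sections then say what confirmation means and what follows without it.

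- 6.2.4 ends treatment, follows the participant for up to two weeks and then ends study participation if "a confirmatory CSF antigen titer is negative by Day 5 AND no positive result from the qualifying CSF culture is obtained through Day 4".
- 6.3.21 makes it a condition of staying in the study that the "qualifying CSF culture must be positive by Day 4 if a confirmatory CSF cryptococcal antigen titer by latex agglutination is not positive by Day 5".
- 6.3.2 (Documentation of CM Status) wants the referring laboratory's positive India ink or antigen result "confirmed within 5 days after study entry by CSF antigen testing from an approved laboratory or with a positive entry CSF culture by Day 5".
- 6.3.18 says: "A negative CSF antigen titer by latex agglutination will not exclude the participant if the entry CSF culture is positive for" *C. neoformans*. It puts no day limit on the culture.
- 8.1 lists as a reason to stop treatment: "Failure to have CM confirmed by Day 5 by testing performed at a DAIDS-approved laboratory".
- 8.2 lists as a reason to leave the study: "Negative screening CSF culture and/or confirmatory HIV status screening results". Where the antigen is negative by Day 5, it defines a negative culture as "a negative culture after 5 days of incubation if there is no yeast found on culture".

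On the day count, 6.2.2 says that the timing of first-week visits "should be based on the first day of treatment (day 1 = first day after first dose of fluconazole or ampho B-based regimen". It allows the first dose up to 72 hours after entry.

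**The concern.** The rules share a purpose: to remove people who turn out not to have CM. They give different last days on which a culture can rescue a participant whose confirmatory antigen is negative. If growth appears between those days, a site following 6.2.4 removes a randomised, dosed participant with culture-proven meningitis. A site following 6.3.2 regards the disease as confirmed.

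Removal affects primary outcomes. Survival is a primary outcome (9.2.1.3) and is not collected after the short follow-up in 6.2.4. The week-2 change in quantitative CSF culture is the primary efficacy measure (Schema; 3.0), and that sample may also be lost.

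**Working it through.** The plan gives no figure to reproduce. The check applies each rule to one test case and then examines the day count.

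**Test case.** Entry on a referring-laboratory result; CSF and first dose both on the day of entry; approved-laboratory antigen negative by Day 5; entry culture first positive on Day 5.

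| Section | Limit | Result |
|---|---|---|
| 6.2.4 | positive culture through Day 4 | off treatment, then off study |
| 6.3.21 | positive culture by Day 4 | may not remain in study |
| 6.3.2 | positive entry culture by Day 5 | CM confirmed |
| 4.1.1, 8.1 | CM confirmed by Day 5 | met, if 6.3.2 defines confirmation |
| 6.3.18 | culture positive, no day given | not excluded by the antigen |
| 8.2 | 5 days of incubation without yeast | not negative, since growth appears at 5 days |

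The two sets of rules agree if the culture grows by Day 4, and also if it has not grown by Day 5. They part only when first growth falls on Day 5.

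**Day count.** Applying the 6.2.2 count to these deadlines, Day n = first dose + n days.

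- CSF and dose on the day of entry: Day 4 is 4 days of incubation, one short of the 5 in 8.2.
- CSF one day before first dose: Day 4 is 4 + 1 = 5 days of incubation, so 6.2.4 and 8.2 agree. The mismatch between 6.2.4 and 6.3.2 remains.
- First dose 0 to 72 hours (0 to 3 days) after entry: Day 5 falls between entry + 5 and entry + 8. The antigen limit in 6.3.2 is entry + 5. Its two limits, given in one sentence, therefore coincide or differ by up to 8 - 5 = 3 days, depending on which count Day 5 uses.

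**What is lost on removal.** Stopping at Day 5 and following for up to 14 days ends contact at about Day 5 + 14 = Day 19. Later survival is not collected. The week-2 window (Days 12 to 17) falls inside this contact period. However, 6.2.4 prescribes only the discontinuation evaluations, for which the schedule of events marks no mandatory culture. Section 6.3.22 says that participants who stop treatment early have CSF collected only as clinically indicated. Against that, 6.3.21 requires a week-2 culture from all participants. Loss is possible but not settled by the text.

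**The case against.** The strongest case is that this is a one-day slip in a rare situation. A case needs a referring-laboratory diagnosis, a negative approved-laboratory antigen and first growth on one particular day. Participants who are removed are still treated by their own physician. Only 6.3.2 expressly accepts a Day 5 culture: 4.1.1 and 8.1 merely set the date for confirmation, 6.3.18 points to 6.2.4 and could be read as subject to it, and the conflict with 8.2 depends on when the CSF was taken. All of this stands, and it limits the severity.

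Two possible defences do not remove the conflict. One is that 6.2.4 governs, but no precedence is stated; 6.3.2 refers to 6.2.4 for how a participant is followed, not for the deadline. The other is that the days run on different clocks, but the protocol never says so, and with the first dose on the day of entry the limits still differ by a day.

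A reader might infer more than the documents support:

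- **A six-day spread of cut-offs.** With CSF 72 hours before entry and dosing 72 hours after it, the limits fall at entry + 2 (8.2), + 5 (6.3.2, antigen), + 7 (6.2.4) and + 8 (6.3.2, culture). This stacks two extremes, although 6.2.2 strongly encourages starting within 24 hours. It mixes antigen and culture limits, and it applies a count written for visits to laboratory deadlines.
- **Certain loss of the week-2 culture.** The sections can be read either way.
- **An unreplaced participant.** The replacement rule in 9.1 applies only while a Stage 1 cohort is open, and 5.1 says Stage 1 is complete.
- **Bias between arms.** The confirmation rule is the same in every arm, and nothing shows a differential effect.

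**Conclusion.** The contradiction holds. For participants entered on a referring-laboratory result whose confirmatory antigen is negative, 6.2.4 and 6.3.21 end treatment and participation unless the culture is positive by Day 4, while 6.3.2 counts a positive entry culture by Day 5 as confirmation. Nothing reconciles the two when CSF and first dose fall on the day of entry.

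The severity is minor. The number affected is not given and is probably very small. For each such participant, survival after about Day 19 is lost and the week-2 culture may be. The Day 19 figure assumes removal on Day 5, the full two weeks of follow-up and the 6.2.2 count. The contradiction itself does not depend on those assumptions. It still merits correction because the rule decides whether someone with proven disease stays on study treatment, and the repair is nearly free.

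**What to change.** Change Day 4 to Day 5 in 6.2.4 and 6.3.21, matching 4.1.1, 6.3.2 and 8.1. State once whether Day 5 counts from entry or from first dose, and use that count for both limits in 6.3.2.

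Two things should stay as they are. Keep the removal of participants whose culture is negative after two weeks of incubation (second bullet of 6.2.4; first branch of the 8.2 definition), because a rule saying only that antigen or culture by Day 5 confirms CM would contradict it. Keep the 8.2 criterion as an incubation time. If it became Day 5 after first dose, incubation could run from 5 days (CSF and dose at entry) to 3 + 8 = 11 days (CSF 72 hours before entry, dose 72 hours after), which changes a laboratory criterion.

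The cost is wording, in a draft that still contains placeholders; no new sample, visit or procedure is needed. The downside is up to one more day of study drug for an antigen-negative participant whose disease is not yet confirmed.

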6.2.5 Evaluations for Study Participants Who Do Not Start Study Treatment

Participants who do not start study treatment within 72 hours after entry must be discontinued from the study. No additional follow up is required. All week 0 forms must be completed and keyed.

- - 1. Study Completion Evaluations

The week 24 evaluations will be completed as the participant’s final on-study visit.

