# SCHEMA

A5225/HiFLAC

A Phase I/II Dose-Finding Study of High-Dose Fluconazole Treatment in AIDS-Associated Cryptococcal Meningitis

DESIGN Overview

A5225/HiFLAC is a phase I/II dose escalation and validation study of the safety, tolerability, and therapeutic effect of an induction-consolidation strategy of high-dose fluconazole alone **or with oral flucytosine (5FC)** for the treatment of cryptococcal meningitis (CM) in HIV-infected participants. As noted in section 2.2, comparison of this study’s results with historical data may be problematic. For this reason, a cohort treated with amphotericin B deoxycholate (which will be referred to as ‘ampho B’ in this study) alone or in combination with 5-fluorocytosine **or fluconazole, according to local standard of care** (**any** of which will be referred to as ‘an ampho B-based regimen’ in this document) will be included in this study.

The study will proceed in two stages (see A5225/HiFLAC Stages 1 & 2 Flow Chart). In Stage 1, Dose Escalation, up to three induction doses of fluconazole **alone** will be tested in sequentially enrolled cohorts. Stage 2, Dose Validation, will not open until the maximum tolerated dose (MTD) of fluconazole has been identified in Stage 1. In Stage 2, induction doses of fluconazole that are found to be safe in Stage 1 will be tested in simultaneously enrolled cohorts. In each stage, participants will be randomized at entry into Step 1. Over the course of the study, participants will register to subsequent steps (Steps 2-4) based on their initial randomization and/or their response to treatment. The study steps are:

- Step 1: Induction therapy with either high dose fluconazole or ampho B
- Step 2: Induction following early ampho B intolerance (only for participants randomized to ampho B treatment in Step 1) (fluconazole at 400-800 mg daily)
- Step 3: Consolidation therapy (fluconazole 400 mg daily)
- Step 4: Maintenance therapy (fluconazole 200 mg daily)

Stage 1 (Dose Escalation)

Stage 1 will include up to three sequentially enrolled cohort sets, each testing a different induction dose of fluconazole and gathering data about ampho B-based treatment (see A5225/HiFLAC Stage 1 Flow Charts #1-3). Each cohort will enroll up to 24 participants randomized to fluconazole and up to 8 participants randomized to an ampho B-based regimen. At any time during the study, enrollment may be halted for safety reasons.

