### 5.3 Pharmacy: Product Supply, Distribution, and Accountability

Fluconazole will be provided by Pfizer.

Neither amphotericin B deoxycholate nor 5-fluorocytosine **or fluconazole for use with amphotericin B deoxycholate** will be provided by the study.

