### 9.2 Outcome Measures

9.2.1 Primary Outcomes

9.2.1.1 Discontinuation of **study-provided** fluconazole or ampho B, including precipitating and surrounding adverse events.

9.2.1.2 Qualitative and quantitative CSF culture results at entry, week 2, and when conducted thereafter.

9.2.1.3 Survival.

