### 9.5 Analysis

9.5.1 Stage 1

Dose escalation is based on DLT and the decision rules as outlined above. As noted above, between-dose comparisons to select the fluconazole dose(s) to carry forward will largely be descriptive and not formally powered as all information will be factored into this decision.

9.5.2 Stage 2

In this pilot, we intend to combine the data over both Stages for the ampho B-based cohorts and for fluconazole doses that are tested in Stage 2. As noted above, only the confidence interval around the observed DLT rate in each dose will be adjusted for the dose escalation scheme. Analyses will employ appropriate methods such as Fisher’s exact test to compare dichotomous outcomes (e.g., Grades 3 and 4 events; CSF clearance before week 10) between doses or drugs, and t-tests or Wilcoxon tests to compare continuous covariates between two groups (or ANOVA or Kruskall-Wallis tests if three groups including ampho B). In the event all three fluconazole doses are evaluated in Stage 2, tests for trend such as ANCOVA, Cochran-Armitage and Jonckheere-Terpstra tests will be performed. Survival and other measures of time-to-event from study entry will be summarized with Kaplan-Meier estimates and, where appropriate, tested with log rank tests and possibly proportional hazards regression. The duration of the initial hospitalization will need to consider the duration of hospitalization preceding study entry. The focused neurological exam will be analyzed both on an item-by-item basis and also as a summary measure using methods such as mixed models analysis of variance or GEE that accommodate missing data and changing covariates.

The content and schedule of reports to be available to the core team, the SMC, and the full team will be detailed in the Study Monitoring Plan that will be developed prior to the opening of accrual to the study.

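### Randomised participants who do not start treatment within 72 hours leave the study with no later vital status, although survival from entry is a primary outcome

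*Protocol*

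**What the plan says.** The Schema fixes the time of randomisation: "In each stage, participants will be randomized at entry into Step 1". Section 6.2.2 then allows up to 72 hours to begin the assigned treatment and encourages a start within 24 hours.

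Section 6.2.5 deals with those who miss the limit: "Participants who do not start study treatment within 72 hours after entry must be discontinued from the study". Their week 0 forms are completed, and for the period after that: "No additional follow up is required". Section 8.2 lists the same event, "Failure to initiate study treatment within 72 hours after entry", as a reason to leave the study, not merely to stop treatment.

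Section 9.2.1 lists "9.2.1.3 Survival" among the three primary outcomes. Section 9.5.2 sets the time origin: "Survival and other measures of time-to-event from study entry will be summarized with Kaplan-Meier estimates". By contrast, section 6.2.4 says of participants who stop treatment early that they "will continue to be followed on study, off treatment per the SoE".

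**The concern.** Randomisation comes before the 72-hour limit, so non-start is a post-randomisation event. The survival clock is already running when the rule takes these participants out. An analysis would have to exclude them or censor them at about day 3. Either choice is harmless only if non-start is unrelated to both arm and prognosis. With open-label assignment that cannot be assumed, because deterioration, refusal or practical difficulty in giving the assigned regimen could each lead to a non-start.

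At stake is the randomised survival comparison, between fluconazole doses and between fluconazole and ampho B. A statistical analysis plan can define the analysis set, but it cannot recover a vital status that was never collected. The rule also sits awkwardly with the rest of the protocol. Those who stop treatment are followed, and even participants found to be HIV-negative or culture-negative are followed for up to two weeks (section 6.2.4). Section 2.1.1 itself warns that losses to follow-up can obscure real treatment differences.

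**Working it through.** **Inputs from the protocol**
- Target of 48 participants per fluconazole dose and 48 on ampho B (9.3.2).
- Design contrast of 50% versus 75% efficacy, 90% power, one-sided alpha 0.10 (9.3.2).
- Illustrative 10-week mortality of 16/64 = 25%, from the South African study of ampho B plus flucytosine cited in 2.1.2. This gives survival s = 0.75.

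**Assumed input**
- Number of non-starters k in a group of 48. The protocol gives no figure, so k = 1, 2, 3 and 5 (2% to 10%) are shown.

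**The plan's own figure**

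n = [z(0.90)·√(2·0.625·0.375) + z(0.90)·√(0.5·0.5 + 0.75·0.25)]² / 0.25²

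= [1.2816 × (0.6847 + 0.6614)]² / 0.0625 = 47.6, so 48 per group.

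Power at 48 per group is 90.2%, which agrees with the stated 90%.

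**Effect on power.** With 5 of 48 lost in one arm, the same calculation gives 88.9%, a fall of 1.3 points. Lost power is not the problem.

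**Effect on what can be estimated.** Suppose observed survival is s among the 48 − k followed participants. Survival in all 48 can then lie anywhere between
- s(48 − k)/48, if every non-starter died, and
- [s(48 − k) + k]/48, if every non-starter lived.

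The width of that range is k/48, whatever s is.

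| k | Lowest | Highest | Width (points) |
|---|---|---|---|
| 1 | 35.25/48 = 73.4% | 36.25/48 = 75.5% | 2.1 |
| 2 | 34.5/48 = 71.9% | 36.5/48 = 76.0% | 4.2 |
| 3 | 33.75/48 = 70.3% | 36.75/48 = 76.6% | 6.3 |
| 5 | 32.25/48 = 67.2% | 37.25/48 = 77.6% | 10.4 |

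For a difference between two groups of 48, the two widths add.

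**Scale.** The sampling standard error of survival in one group is √(0.25 × 0.75/48) = 6.25 points. With k = 2, the largest error relative to the observed 75% is 75.0 − 71.9 = 3.1 points, half a standard error. With k = 5 it is 75.0 − 67.2 = 7.8 points, more than one standard error. Unlike sampling error, this error has a direction that the data cannot reveal.

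**The case against.** A reader might infer that non-start is likelier on ampho B, so that the rule flatters that arm. Ampho B is intravenous, and section 5.3 says "Neither amphotericin B deoxycholate nor 5-fluorocytosine" is among the products the study supplies, whereas study fluconazole is a supplied oral tablet. The protocol does not support that conclusion. It gives no non-start rate for any arm. Criterion 4.1.15 requires at least two weeks of the regimen to be available at the site, and section 2.2 restricts participation to sites with access to ampho B, in settings where it is predominantly standard care. The 72-hour rule applies equally to every arm. A difference by arm remains possible through intravenous access or open-label preference, but it is not shown, and neither is its direction.

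A reader might also point to the expected very early mortality of up to 15% in section 9.3.1 to argue that non-starters are at high risk. That figure covers deaths before Day 4. Someone alive and untreated at 72 hours has passed most of that window, so the figure says little about risk after exit, which is the period that goes unobserved.

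Nor does all data collection stop. Week 0 forms are completed, and section 6.2.4 generally asks for discontinuation evaluations at study exit, though the more specific section 6.2.5 may override that. What is clearly missing is vital status after exit.

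Other points on this side stand. This is a phase I/II pilot whose first primary objective is the MTD. The survival hypothesis (1.1.2.2) compares fluconazole doses, which share route and supply. Some non-starters will have withdrawn consent and could not be followed in any case; section 9.1 already replaces refusals and withdrawals before any drug while a Stage 1 cohort is open. With one or two non-starters, the possible error is well inside sampling error. These points limit the weight of the concern. They do not justify leaving vital status uncollected for consenting participants.

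**Conclusion.** The concern holds as a minor one. Sections 6.2.5 and 8.2 remove randomised participants after randomisation with no later vital status, while survival from entry is a primary outcome. Any effect on the survival comparison could not be checked or repaired. In a group of 48 the unidentified part is 2.1 points per non-starter, or 2.1 to 10.4 points for an assumed 1 to 5. The widths depend only on k and 48; the ranges around 75% also depend on the borrowed 25% mortality. The actual number of non-starters is unknown and may be zero, in which case nothing is lost. No direction of bias, and no disadvantage or advantage to the ampho B arm, can be claimed from the protocol.

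**What to change.** Amend both 6.2.5 and 8.2; changing only one would leave the other still ending study participation. For randomised participants whose HIV and CM status is confirmed but who do not start treatment in time, collect vital status at weeks 10 and 24 by telephone or from records, unless consent is withdrawn. Report the number of non-starts by arm, with reasons, and analyse survival as randomised. The DLT evaluation may stay restricted to treated participants. The 72-hour treatment rule, clinical care, sample size and stated power are unchanged.

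The cost is a short amendment to two sections and a few extra contacts. Participants who withdraw consent will remain unknown; for them, a best-case and worst-case range like the one above can be reported.
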